## Abstract

**Background:**

Non-specific chronic low back pain (NSCLBP) has become a significant problem due to high healthcare utilization, rising costs of care and perceived limitations of effectiveness of many current treatments. Systematic reviews have repeatedly concluded that, on average across participants, exercise for NSCLBP appears effective in decreasing pain and improving function. Not all people with NSCLBP benefit from exercise programs and it would assist care-providers and care-seekers if factors that impact on program effectiveness and success were identified.

**Methods and design:**

The study will be a randomised controlled trial comparing an exercise rehabilitation program informed by a participant preferences questionnaire compared to a program without this guideline for patients with chronic low back pain. A sample of 150 patients will be recruited in Melbourne, Australia through community-based healthcare clinics that provide supervised exercise rehabilitation programs for people with non-specific chronic low back pain. Clinicians will be randomly assigned to exercise preferences questionnaire or no questionnaire and participants will be allocated in a concealed manner. A qualitative focus group study of exercise instructor feedback about the exercise preferences instrument will be embedded in the research design. Two qualitative focus group studies will also be conducted for participants in the intervention and the control groups to obtain feedback about participants' experiences of the two types of exercise programs. The primary outcomes will be functional ability, pain, fear avoidance, exercise adherence.

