### Quantitative study

#### • Design

The study will be a randomised controlled trial (RCT) with an intervention period of six weeks and exercise programs will be those of usual clinician practice. Outcomes will be measured at baseline and at 6, 12, 26 and 52 weeks from baseline.

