### Sample Size

A total of 120 patients (60 questionnaire group, 60 no questionnaire group) will be required for 80% power to detect a 5 point reduction on 100 point measure of function with 95% confidence using a two-tail test of difference between group means when raw scores have an estimated standard deviation of 10/100 points). We will allow for a 10% loss to follow-up and aim to recruit 75 participants per group. This will enable collection of data for at least 85% of enrolled participants.

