### Outcome measures

Socio-demographic data including age, back pain history and occupation status, will be collected at baseline. The following outcomes will be assessed at baseline, at completion of the 6 week intervention and at 12, 26 and 52 weeks: Functional ability: Oswestry Disability Index (ODI) [28], Pain: Tagged Numeric Pain Scale (NPS) [29], Fear avoidance: Fear Avoidance Beliefs Questionnaire (FABQ) [30]. The Exercise Preferences Questionnaire will be completed at baseline only and the Exercise Diary will be completed after each exercise session during the intervention and follow-up period. Time to complete the Exercise Preferences Questionnaire will be evaluated by asking the participant to note the time taken on page two of this form. Follow-up reminders will be given by phone or SMS and completed outcome measures returned by pre-paid envelope or SMS.

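### Four unranked primary outcomes and no primary time point, while the sample size supports a single comparison on function

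*Protocol article*

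**What the plan says.** The Abstract (Methods and design) names four primary outcomes without ranking them: "The primary outcomes will be functional ability, pain, fear avoidance, exercise adherence". The body of the article lists the measures but sets no order among them, so nothing there narrows the Abstract.

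The Design paragraph sets the schedule: "Outcomes will be measured at baseline and at 6, 12, 26 and 52 weeks from baseline". Outcome measures ties three instruments to it: ODI for function, the numeric scale (NPS) for pain and the FABQ for fear avoidance, collected "at baseline, at completion of the 6 week intervention and at 12, 26 and 52 weeks". Neither section says which follow-up time decides the trial. Adherence is not on that list. The nearest source of adherence data is a diary: "the Exercise Diary will be completed after each exercise session during the intervention and follow-up period". No visit-by-visit adherence test is described.

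Data Analysis plans t tests or Mann-Whitney tests between groups, and ANCOVA where baseline is related to outcome. It gives effect sizes with 95% intervals for pain and function. It states no level for the tests and does not say which result is decisive.

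Sample Size calls for 60 patients per group, giving "80% power to detect a 5 point reduction on 100 point measure of function". The section sets the level at 95% confidence, two-tailed, and puts the standard deviation at 10. It then sets recruitment at 75 per group with 10% loss allowed for.

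**The concern.** The declared primary set and the sample size do not match. The trial has four primary outcomes, three of them measured at four follow-up times, but its error rate and power are set out for one test on one of them.

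Two separate consequences follow:

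- **False positives.** With several primary comparisons each judged at 5% and no stated decisive one, a significant result on any of them could be presented as a positive trial. The chance that at least one arises by luck is then above 5%.
- **Missed effects.** The 80% power describes function only. The article makes no power statement for pain, fear avoidance or adherence, and the power for function falls if the 5% has to be shared.

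The choice of deciding outcome and time determines the sample size, so it belongs in the protocol. A multiplicity rule added later in an analysis plan could restore the error rate but not the power.

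**Working it through.** **Inputs from the article.** Four primary outcomes (Abstract). Four follow-up times (Design). Three scales tied to those times, plus a per-session diary (Outcome measures). Difference 5, SD 10, 80% power, 95% confidence two-tailed, 60 per group, 75 per group recruited, 10% loss (Sample Size).

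**Inputs assumed.** Each test at two-sided 5%, inferred from the 95% confidence in Sample Size and the 95% intervals in Data Analysis. No true effect on any outcome. Correlation 0.3 to 0.7 between outcomes and 0.5 to 0.8 between visits. The article gives no correlations, so these are shown as ranges.

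**1. The plan's own sample size.** Normal approximation, per group:

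n = 2 × (1.960 + 0.842)² × (10/5)² ≈ 62.8, so 63 per group (126 in total); the exact t test gives 64 (128).

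The stated 120 is slightly short of this. At 60 per group, power is Φ(0.5 × √(60/2) − 1.960) = Φ(0.779) = 78.2%, or 77.5% by the exact t test. The recruitment target covers the gap: 75 × 0.9 = 67.5, and 67 per group gives about 82% by the t test. This is enough for one function comparison at 5%, and that is all it covers.

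**2. Number of comparisons the text supports.** 3 scales × 4 times = 12, plus one for adherence = 13. At a single visit there are four.

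**3. Chance of at least one false positive, independent tests.** 1 − 0.95^k:

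- k = 4: 18.5%
- k = 12: 46.0%
- k = 13: 48.7%

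**4. The same with correlation.** This was simulated from multivariate normal test statistics. The correlation between two comparisons is the product of the between-outcome and between-visit values. The adherence comparison is treated as a fourth outcome measured at one visit.

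| Between outcomes | Four outcomes, one visit | 13 comparisons, between-visit 0.5 | 0.7 | 0.8 |
|---|---|---|---|---|
| 0.3 | 17.3% | 41.0% | 35.7% | 32.1% |
| 0.5 | 15.7% | 37.7% | 32.5% | 29.2% |
| 0.7 | 13.0% | 33.1% | 28.0% | 25.0% |

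**5. Power for function if all four stay primary.** Holm's first step across four outcomes at one visit uses 0.05/4 = 0.0125, with critical value 2.498. Power is Φ(0.5 × √(n/2) − 2.498):

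- n = 60: Φ(2.739 − 2.498) = 59.5%
- n = 67: Φ(2.894 − 2.498) ≈ 65%
- n = 75: Φ(3.062 − 2.498) = 71.4%

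Reaching 80% at this level needs 90 per group before dropout. These figures make no allowance for clustering by clinician.

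**The case against.** The strongest reply is that this is a condensed article and no analysis plan is shown. Multiplicity procedures are commonly left to that plan. The trial is sized on function, so a reader could take function as the lead outcome. The reply holds in part: the lack of a multiplicity rule is not a defect in itself, and it is not counted as one here. What remains is what the article does state: four outcomes called primary on equal terms, and a sample size that fits one of them. Sizing on function hints at a lead outcome but does not make it the only primary one, and it leaves the follow-up time open.

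Some stronger conclusions are tempting, but the article does not support them:

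- **Sixteen tests and a false positive more likely than not.** Four outcomes by four times gives 1 − 0.95^16 = 56%. Adherence is not tied to the four visits, however, so 16 is not a firm count. The figure also needs independence, which is implausible for repeated measures on the same patients. Carrying the last score forward makes visits more alike still.
- **Lack of power for the other outcomes causes false positives.** It does not; it bears on missed effects.
- **A 5% level for each test and an any-one-wins rule as stated facts.** The level is inferred. The success rule is neither stated nor excluded.
- **A trial that can give no clear answer.** This is too strong. The function comparison is planned and sized, and it can be read on its own terms once it is named as decisive.

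**Conclusion.** The point holds as a mismatch between the declared primary outcomes and the basis of the sample size. If any one significant primary result may count as success, the family-wise error is about 13% to 17% for four outcomes at a single visit, and about 25% to 41% for the 13 comparisons that the text supports. The lowest of these is more than twice the nominal 5%, and the full set runs to several times it. The sizes rest on the assumed correlations, on tests at two-sided 5% and on no true effect anywhere; independence gives 18.5% and 48.7%. The power statement is a separate matter and covers function only. The data remain usable and the remedy is simple, so this should be corrected but does not invalidate the trial.

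**What to change.** Name one primary endpoint that matches the sample size: ODI at one stated follow-up time, tested at two-sided 5% with the between-group analysis the plan prespecifies. Make pain, FABQ, adherence and the other time points secondary. This keeps the stated error level and needs no extra patients. It costs a change of wording in the protocol and any registration, made before unblinding. The downside is that the other outcomes lose a stand-alone confirmatory claim.

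If the sponsor wants all four to stay primary, apply Holm across them at one stated time point, define how the diary yields the adherence measure at that point, and restate the power. That option is not free. At the first-step level, function power is about 60% at 60 per group, 65% at the 67 expected after loss and 71% at 75. Restoring 80% would take 90 per group before dropout (180 in total), above the planned 75, and any allowance for clustering by clinician would come on top.

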**Discussion:**

This trial will evaluate the effectiveness of individualised exercise prescription compared to usual exercise prescription for NSCLP and, using feedback following the trial, refine the exercise preferences questionnaire.

## Background

Non-specific chronic low back pain (NSCLBP) has become a significant problem due to high healthcare utilization, rising costs of care and perceived limitations of effectiveness of many current treatments. It is a significant source of long-term disability and absence from work and a substantial burden in industrialized societies [1-9]. NSCLBP is not a diagnosis but rather a description of back pain for which a cause cannot be definitively identified and a precise patho-anatomical diagnosis cannot be given. This accounts for approximately 85% of all low back pain and does presume that specific pathologies, such as nerve root compression or tumour, have been ruled out by appropriate tests and imaging [10]. The condition manifests as a continuation of an initial episode or periodic recurrences and remissions [11,12].

Systematic reviews have repeatedly concluded that, on average across participants, exercise for NSCLBP appears effective in decreasing pain and improving function [13-20]. Many exercise programs have been designed and quite different programs appear to have similar effects. Not all people with NSCLBP benefit from exercise programs and it would assist care-providers and care-seekers if factors that impact on program effectiveness and success were identified [21,22]. Clarification of the ingredients that make exercise programs enjoyable and inviting would enable clinicians to prescribe interventions that are appropriate for the NSCLBP care-seeking population. A systematic search of the literature demonstrated that there is no available instrument that measures patient experience of exercise rehabilitation programs for NSCLBP. It is currently unknown whether patient expectations are met or what they experience during exercise programs for NSCLBP.

Following Monash University Standing Committee on Ethics in Research Involving Humans (SCERH) approval (SCERH CF07/1854 – 2007/0558), we conducted qualitative focus group research of participant experience of exercise programs for NSCLBP and factors that they perceived important for engagement and participation. The results of this study indicated that people with NSCLBP have a range of environmental and exercise design preferences that are important to consider in exercise prescription. Enablers for exercise participation included shared decision-making, effective communication, a history of exercise ability and participation, familiarity with exercise environments and the fitness culture, individualised and supervised programs, use of preferred environments, family support, variety and fun, motivation strategies and education. Barriers included time constraints, cost, boring programs, symptom aggravation, consequences of stigma, dissatisfaction with formal exercise and gym 'culture' [23-25].

A decision-aid for exercise prescription is currently not available and the results of our qualitative research have informed the development of a questionnaire that clinicians can use to determine participant exercise preferences and inform their practice of exercise prescription. This questionnaire requires testing in the clinical environment to determine its utility as a method of systematic evaluation of care-seeker needs and preferences related to exercise. The research plan is to implement the questionnaire in a range of exercise programs that are specific to NSCLBP, evaluate the effectiveness of individualised exercise prescription and evaluate feedback about the instrument.

## Methods/Design

Monash University SCERH has granted approval for this study (CF08/2015 – 2008000990). The trial will be reported according to the recommendations of the CONSORT Statement [26,27] and the flow of participants through the study is represented in Figure 1. The quantitative study will compare an exercise rehabilitation program informed by a participant preferences questionnaire compared to a program without this guideline for patients with NSCLBP. The qualitative study will evaluate clinician and participant experience. Patients presenting for exercise prescription will be allocated to clinicians who either do or do not use information regarding patient exercise preferences.

**Figure 1 F1:**
[figure not shown]
**Participant flow through the RCT (based on CONSORT Statement)**.

### Quantitative study

#### • Design

The study will be a randomised controlled trial (RCT) with an intervention period of six weeks and exercise programs will be those of usual clinician practice. Outcomes will be measured at baseline and at 6, 12, 26 and 52 weeks from baseline.

#### • Controlling bias

The RCT design includes key method features that have been recognised as important in minimising bias in clinical trials: true randomisation, concealed allocation, specification of eligibility criteria, blind outcome assessment, blind analysis and intention-to-treat analysis.

#### • Setting

A sample of patients will be recruited in Melbourne, Australia through community-based healthcare clinics that provide supervised exercise rehabilitation programs for people with NSCLBP.

#### • Protocol protection

The following mechanisms will be used to ensure that the trial protocol is applied consistently: protocol manuals will be developed and all involved researchers will be trained to ensure that screening, assessment, random allocation and treatment procedures are conducted according to the protocol; a random sample of treatment sessions will be audited to check that treatment is administered as per the protocol.

### Study population and recruitment

#### • Clinics and clinicians

The study will be conducted in Melbourne metropolitan primary health care clinics that provide exercise programs for rehabilitation of musculoskeletal conditions. The contact details used will be those publicly available in the telephone directory or online at professional association websites. The clinics will be approached by telephone or email/mail advertisement seeking expressions of interest in research participation.

A phone conversation or meeting will be scheduled with the practice principal to outline the project and distribute the Explanatory statement and Clinic Consent Form. After receipt of signed Clinic Consent, information sessions will be scheduled to address clinicians and inform them of the research background and aims. They will be given an Explanatory Statement to read and keep and a Clinician Consent Form to sign and return to the researcher if they wish to participate. Reception staff in-service training will also be conducted to familiarize clinic staff with the recruitment process, paperwork completion and filing.

#### • Patients

The opportunity to participate will be offered to every eligible consecutive low back pain patient in order of contact until adequate numbers of participants are achieved. Clinic reception staff who are not aware of the research protocol or aims will approach potential participants who are patients seeking treatment for low back pain and use a screening checklist to determine eligibility and interest. They will record the number of patients invited, the number who decline, ineligible patients and reasons [see Additional file 1].

### Concealment

#### • Patients and receptionists

If patients are eligible and interested, reception staff will give them the Explanatory Statement to read and keep and a Consent Form that they will sign and return to the receptionist for filing. Following signed consent participants will complete coded outcome measures and exercise preference questionnaires and return them sealed to reception staff for storage in a secure box for retrieval by the researcher. The completed exercise preferences questionnaire will be put in a sealed envelope, marked EQ, and forwarded to the treating clinician. The envelope will only be opened by the clinicians allocated to the questionnaire group. Reception staff and patients will not know which practitioners have been allocated to use the completed exercise preference questionnaire to guide exercise prescription or to the control group.

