### Randomization

#### • Clinicians

Clinicians who have consented to participate will be randomly allocated, by computer-generated codes (code: exercise questionnaire group (EQ); no exercise questionnaire group (NQ)) in sealed opaque envelopes, to one of two groups with stratification to allow equal representation of qualifications. These codes will be generated by an independent researcher who has no contact with trial participants. Group 1 clinicians allocated to use the exercise preferences questionnaire will use the responses to the exercise preferences questionnaire to inform their exercise prescription. Group 2 clinicians do not use the exercise preferences questionnaire and will return the unopened envelope to a secure storage box in the reception area. These clinicians will prescribe exercise according to their usual practice.

The two groups of clinicians will not disclose their group allocation or any details or findings of the questionnaire. A code-breaker master document will be kept in a locked location at the university and cannot be viewed by reception staff or clinicians.

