### Blinding

#### • Clinicians

The clinicians will be asked to agree not to disclose group allocation or questionnaire details to patients, colleagues or researchers.

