#### • Patients

The plain language Explanatory Statement and Patient Consent Form will inform participants that they have an equal chance of receiving one of two acceptable exercise prescription methods.

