#### • Assessor

A blinded examiner will perform all outcome assessments. Participants will be asked to refrain from discussing their treatment with the outcome assessor. At trial completion, participants will be asked to nominate whether they had been in the experimental or control group. The data manager and statistician will be unaware of treatment allocation until completion of analyses.

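### The plan states as fact that patients and reception staff will not know a clinician's arm, but its procedures do not assure this, and the primary outcomes come from the patients

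*Protocol article*

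**What the plan says.** Under Concealment (Patients and receptionists) the article makes an unqualified statement: "Reception staff and patients will not know which practitioners have been allocated to use the completed exercise preference questionnaire to guide exercise prescription". The same paragraph and the sections on Randomization and Blinding describe the procedure behind it.

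- All participants fill in the form before treatment: "Following signed consent participants will complete coded outcome measures and exercise preference questionnaires and return them sealed to reception staff".
- The completed form goes to the treating clinician in a sealed, marked envelope. "The envelope will only be opened by the clinicians allocated to the questionnaire group".
- Questionnaire-group clinicians "will use the responses to the exercise preferences questionnaire to inform their exercise prescription". Control clinicians send the envelope back unopened to a storage box in the reception area, and "These clinicians will prescribe exercise according to their usual practice".
- On disclosure: "The clinicians will be asked to agree not to disclose group allocation or questionnaire details to patients, colleagues or researchers".
- Patients are told that "they have an equal chance of receiving one of two acceptable exercise prescription methods".
- Under Blinding (Assessor), a blinded examiner is to carry out every outcome assessment. The same section adds: "At trial completion, participants will be asked to nominate whether they had been in the experimental or control group".

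The abstract names function, pain, fear avoidance and adherence as primary outcomes. Under Outcome measures, follow-up measures come back by pre-paid envelope or SMS, and an exercise diary is filled in after each session.

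**The concern.** The intervention is a prescription shaped by the patient's own written answers, so the patient knows one half of the comparison and then experiences the other half. The more the questionnaire changes practice, the easier it becomes to infer the arm. A rule on what clinicians say does not reach what a patient recognises.

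The stated envelope procedure also differs by arm after the consultation. An unopened envelope returned to the reception area points to a control clinician, and reception staff are the other group declared unaware. They also screen and invite patients, so what they learn is not harmless.

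At stake is the meaning of a between-group difference. A patient who believes that their wishes were used, or ignored, may rate function, pain or fear avoidance differently for that reason alone. The analysis would count that shift as an effect of preference-informed prescription. A trial report that repeated the masking statement and the claim of blind outcome assessment would promise more protection than the design gives.

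**Working it through.** The plan gives no figure on this point, so the main check sets each safeguard against the routes by which the arm could become known.

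| Safeguard (section) | What it does | What it leaves open |
|---|---|---|
| Same form completed in both arms (Concealment) | Completing it reveals nothing about the arm | The patient knows what they wrote |
| Sealed envelope to every treating clinician (Concealment) | Its arrival looks the same in both arms | Its return is described for controls only, unopened (Randomization) |
| Clinicians do not disclose (Randomization; Blinding, Clinicians) | Limits what is said | Does not limit recognition of one's own preferences in the programme |
| Neutral information (Blinding, Patients) | Does not label either method as better | Tells patients that there are two methods |
| End-of-trial guess (Blinding, Assessor) | Measures unmasking afterwards | Does not prevent it; the article states no use for the answers |
| Blinded examiner (Blinding, Assessor) | Keeps staff judgement out of scoring | The patient supplies the rating, by post or SMS (Outcome measures) |

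Each safeguard is real, but none closes the route through the patient's own answers. The return step adds a separate cue for reception staff.

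**Illustration of scale. The shift is an assumption; the documents give none.**

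Inputs:
- SD 10 and target difference 5 points on a 100-point measure (Sample Size).
- 75 recruited per group less 10% loss (Sample Size): 75 × 0.90 = 67.5, taken as 67.
- Two-sided 5% t test, patients treated as independent, no true effect.
- Assumed shift in mean reported function from knowing the arm: 1 or 2 points, that is 1/5 = 20% or 2/5 = 40% of the target.

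Steps:
1. Standard error of the difference = 10 × √(2/67) = 1.728.
2. Noncentrality = shift / SE: 1/1.728 = 0.579; 2/1.728 = 1.158.
3. Probability that a noncentral t on 2 × 67 − 2 = 132 degrees of freedom lies beyond ±1.978:

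| Per group | No shift | 1 point | 2 points |
|---|---|---|---|
| 60 (stated requirement) | 5% | 8.4% | 19.2% |
| 67 (75 less 10%) | 5% | 8.9% | 21.0% |
| 75 (recruitment target) | 5% | 9.3% | 22.9% |

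The result depends little on which group size is used and almost wholly on the assumed shift.

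**The case against.** The strongest reply is that the plan takes masking seriously and does not take it for granted. Both arms complete the same form, every clinician receives the same sealed envelope, clinicians agree to stay silent, the patient information is neutral, and patients are asked at the end which group they were in. A patient sees one programme and has no comparator. Usual practice may match their wishes through ordinary conversation, so neither a match nor a mismatch proves the arm. The bias list under Controlling bias claims concealed allocation, blind outcome assessment and blind analysis, and does not claim patient blinding. The numerical shift is assumed.

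Much of this stands, and it rules out stronger readings that a reader might infer:

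- *That patients will know their arm, so that masking fails.* The documents do not show this. They show only that masking is not assured.
- *That completing the form, or the marked envelope, gives the arm away.* Both are common to the two arms and work as masking devices.
- *That the envelope is opened, or left sealed, in front of the patient.* The article does not say where this happens. Such detail is commonly left to the full protocol or to the manuals mentioned under Protocol protection, so the silence is no finding.

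What the reply does not remove is the stated text. The masking sentence is categorical, while the plan elsewhere treats the patient's belief as something to ask about. The unopened return by control clinicians is written down. Even if a fuller document adds a return for the other arm, an opened and an unopened envelope would still look different unless resealed or covered. And blind outcome assessment, which the bias list does claim, depends on the patient's unawareness when the patient supplies the rating.

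**Conclusion.** The point holds in a limited form. The article asserts as certain that patients and reception staff will not know the allocation, and its procedures do not secure this. One route, recognition of one's own preferences in the programme, comes with the intervention and can only be acknowledged. The other, the one-sided return of unopened envelopes to the reception area, is avoidable. The examiner's blinding does not protect outcomes that patients complete themselves.

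The size of any bias is unknown and could be nil. The rise from 5% to about 9–21% holds only if knowledge of the arm moves mean reported function by 1 to 2 points, with SD 10, 67 per group and no true effect. It shows that a shift well below the 5-point target would matter, and is not evidence that one will occur. The change is worth making because it corrects a stated procedure and limits what the trial may claim, at very little cost.

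**What to change.** 1. Under Concealment and Randomization, have both arms handle and return the envelope in the same way. For example, every clinician returns it in an identical opaque cover, resealed where it was opened, out of sight of patients and reception staff.
2. Replace the masking sentence under Concealment with: 'patients and reception staff are not told the allocation, but patients may infer it'.
3. State that the end-of-trial allocation guesses will be reported by arm alongside the self-reported primary outcomes.
4. Do not describe those outcomes as blind-assessed. Qualify the blind-assessment entry under Controlling bias and the text under Blinding (Assessor) accordingly.

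The cost is a few sentences in the protocol and the clinician manual, with no extra staff or visits. The downside is a weaker masking claim. Identical envelope handling removes the avoidable cue only; patients may still infer the arm from the programme itself.
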